##### Observation of health promotion talks

Fieldworkers based at facilities will be tasked with observing the delivery of the health promotion talks and completing a checklist to assess (i) the extent to which the talks are adopted at facilities, (ii) whether the talks are being delivered as intended, and (iii) the extent to which the talks are accessed by the pregnant women.

##### Cohort study

At baseline, pregnant women attending the clinic for their first antenatal visit will be screened by fieldworkers, in their home language, for the presence of CMDs and experiences of domestic violence. All women who screen positive — i.e. score ≥13 on the EPDS or ≥2 on the bespoke violence screening tool — will be invited to participate in the cohort study. A random sample of 33% of pregnant women who screen negative (identified by Redcap, using a randomisation table) will also be invited to participate in the cohort study. Fieldworkers will administer several questionnaires assessing risk factors for CMDs and the frequency of domestic violence. The presence of and risk factors for CMDs and experiences of domestic violence in cohort participants will be assessed again at the 36-week gestation and the 6-week postnatal follow-up timepoints. Changes in clinical outcomes and their risk factors will be assessed by comparing the 36-week gestation and the 6-week postnatal outcomes to the baseline outcomes.

The cohort study will be used (i) to assess the presence of and risk factors for CMDs and experiences of domestic violence in pregnant women and (ii) to assess whether the HSS interventions resulted in improvement in clinical outcomes. It will be based on the proportion of women showing a clinically significant improvement as measured by the EPDS. Women with an EPDS score of ≥13 at baseline will be classified as having symptoms of CMD. Clinically significant improvement will be classified as having a 50% reduction in EPDS scores measured at the 36-week gestation and 6-week postnatal follow-up timepoints, compared to baseline. The study will also assess the feasibility of administering these instruments and effectively following up perinatal women in these communities, for a potential future cRCT.

Sample size calculations were used to determine the number of participants needed for a cluster randomised control trial (cRCT). Based on a level of significance (alpha) = 0.05, an intra-cluster correlation coefficient (ICC) = 0.02, an effect size = 0.27, the correlation coefficient between baseline and follow-up (*r*) = 0.3–0.5, and power = 80–90%, 225–291 participants would be needed at each of the intervention and control facilities in a cRCT. For this pilot study at three facilities, we intend to recruit 225–291 participants per facility. If we are able to recruit 20 perinatal women per week at each facility, we would need to spend at least 3 months doing recruitment.

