##### Addressing low levels of detection

Training, delivery of individual-level care, and audit and feedback were selected as the HSS interventions to address the low levels of detection. ANC nurses will be trained to screen all pregnant women for symptoms of CMDs and experiences of domestic violence as part of routine care, using the mental health screening questionnaire [12] available in the MCR [11] and the PACK guidelines [26]. The training material was developed in conjunction with the Knowledge Translation Unit (KTU), a clinical research unit at the University of Cape Town, that led the development of PACK. The PACK guide was used as the foundation for the detection and referral process. A *PACK Antenatal Women and Mental Health Module* [27] was developed to strengthen the mental health component of routinely provided antenatal care. Four case studies formed the backbone of the module, complemented by HSS discussions, completion of relevant stationery, and a focus on effective communication strategies. PACK facility trainers were the recipients of the master training and will be tasked with training ANC nurses at their facilities. The cascaded training will consist of four, weekly, 2-hr training sessions.

During the implementation phase, audit and feedback will be used to assess the screening rates at facilities and provide feedback to the relevant ANC nurses and their managers at bi-monthly meetings.

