Observation of health promotion talks	Assess uptake, fidelity, penetration, and sustainability of health promotion talks	Checklist to be completed by fieldworkers observing the talks		During the delivery of health promotion talks
Cohort study	Assess the presence of and risk factors for CMDs and experiences of domestic violence; assess whether the HSS interventions to improve awareness, detection, referral, and treatment resulted in improvement in clinical outcomes	Interviewer-administered questionnaires: Edinburgh postnatal depression scale [34]; psychological distress screening tool [12]; bespoke questionnaire to assess domestic violence; Household Food Insecurity and Access Scale [35]; Composite Abuse Scale [36]; WHO Disability Assessment Schedule [37]; Multidimensional Scale of Perceived Social Support [38]; Mother-to-Infant Bonding Scale [39]	Pregnant and postnatal women attending antenatal care clinics	Three timepoints — (1) when pregnant women are recruited, (2) when participants are 36 weeks pregnant, and (3) 6 weeks after participants have given birth
Patient file reviews	Assess changes in detection and referral rates of pregnant women with CMDs and experiences of domestic violence	Maternity case record [11]	Pregnant and postnatal women attending MOUs and BANC clinics	Weekly during the implementation phase
Documentation review	Assess coverage of the detection, referral, and treatment interventions	Bespoke patient registers and tracking forms	ANC nurses and OTLs	Daily during the intervention period
Counselling competence	Assess fidelity to the structured counselling format and content	Enhancing assessment of common therapeutic factors tool [40]; bespoke counselling evaluation form	Community health workers (CHWs)	During the last 2 months of the intervention
Qualitative assessments	Assess the acceptability, appropriateness, satisfaction, and feasibility of the selected HSS interventions	Topic guides for key informant interviews and focus group discussions	Pregnant and postnatal women involved in the intervention Healthcare workers involved in the intervention	During the last 3 months of the intervention

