##### Patient survey

During the baseline data collection period (prior to delivering the HSS interventions), pregnant women awaiting their routine tests and consultations will be approached and asked to complete a self-administered survey questionnaire, available in their home language. During the implementation phase, pregnant women who received the health promotion talk will be asked to complete the same survey questionnaire immediately after the talk has been delivered. The survey questionnaire will consist of a few demographic questions; questions about their knowledge of depression, anxiety, and domestic violence; questions on attitudes towards people with mental illness and experiences of domestic violence; and questions on their health-seeking behaviour. We anticipate that 15 to 30 pregnant women will be willing to complete the survey after a talk and plan on administering the survey daily during the 2 weeks of baseline data collection and at least once per week during the implementation phase. The survey will be used to assess the effect of the health promotion talks in changing the mental health knowledge, attitudes, and health-seeking behaviour of perinatal women.

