##### Patient file reviews

During the baseline data collection period and throughout the implementation phase, fieldworkers will capture the outcome of the psychological distress questionnaire found in the MCRs of pregnant women attending healthcare facilities. The information obtained will be used to assess whether delivering the HSS interventions improved (i) detection and referral rates, (ii) uptake of the detection and referral interventions, and (iii) the sustainability of the detection and referral interventions.

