##### Documentation reviews

Reviewing registers and referral forms will be used to assess the coverage of the detection, referral, and treatment interventions. Rates of detection and referral for women with CMDs and experiences of domestic violence will be assessed before the intervention, and monitored weekly throughout the intervention period, by triangulating information obtained from (i) a review of the daily patient registers completed by ANC nurses and (ii) reviewing the referral forms completed by ANC nurses for patients who screen positive and agree to counselling.

The proportion of perinatal women with CMDs and experiences of domestic violence who take up the referral and receive partial or full treatment will be assessed by triangulating information obtained from reviewing the referral and counselling feedback forms to be completed by OTLs for all patients who are referred for the task-sharing psychological counselling programme.

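### Nurse detection and referral rates are compared before and during the intervention without separating women whom fieldworkers had already screened for the same conditions

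*Protocol article*

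**What the plan says.** Under Cohort study, "pregnant women attending the clinic for their first antenatal visit will be screened by fieldworkers, in their home language", for common mental disorders (CMDs) and domestic violence. All women who screen positive and a random 33% of those who screen negative are then invited, so more women are screened than enrolled. Table 2 lists among the cohort instruments the "Edinburgh postnatal depression scale [34]; psychological distress screening tool [12]; bespoke questionnaire to assess domestic violence". Nurses are to screen "using the mental health screening questionnaire [12] available in the MCR [11" (MCR is the Maternity Case Record), per Addressing low levels of detection.

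Nurse performance is measured at the same facilities. Under Patient file reviews, "fieldworkers will capture the outcome of the psychological distress questionnaire found in the MCRs of pregnant women attending healthcare facilities", at baseline and throughout implementation. The purpose is to judge whether the interventions improved detection and referral, their uptake, and "iii) the sustainability of the detection and referral interventions". Under Documentation reviews, detection and referral rates "will be assessed before the intervention, and monitored weekly throughout the intervention period", using nurse registers and nurse-completed referral forms.

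On timing, the Patient survey section says the team "plan on administering the survey daily during the 2 weeks of baseline data collection", and the Cohort study section says that at 20 women per week "we would need to spend at least 3 months doing recruitment". Implementation runs from April to December 2021. Data analyses adjusts implementation outcomes for clinic and relevant confounders; research-screen status is not named.

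**The concern.** There is no control facility, so the before-after contrast carries the inference that the programme changed what nurses detect and refer. If a fieldworker has just asked a woman about distress and abuse, she may be readier to disclose to the nurse, or a referral may come about informally. The nurse record would then partly reflect the research screen. This matters when the share of women exposed differs between periods, and the planned rates give no way to see it.

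Two readings are at stake: the size of the before-after change, and sustainability, because a decline when recruitment ends could come from the withdrawal of the research screen and not from fading nurse practice. A future cluster randomised trial would want to know what nurses detect when no fieldworker has asked first.

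**Working it through.** **Plan's own figure.** The target is 225 to 291 women per facility at 20 per week: 225/20 = 11.25 weeks and 291/20 = 14.55 weeks (2.6 to 3.3 months). The stated 3 months lies in this range.

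**Share of implementation covered.** 1 April to 31 December 2021 is 275 days, or 39.3 weeks. 11.25/39.3 = 0.286 and 14.55/39.3 = 0.370. If recruitment starts with implementation, 39.3 - 14.55 = 24.7 to 39.3 - 11.25 = 28.0 weeks follow without it. The article does not say when cohort screening starts relative to the two baseline weeks.

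**Research-screened share of first visits over implementation (s1).**
- If every first-visit woman is screened during recruitment: 0.286 to 0.370.
- At an assumed 300 first visits a month (69.2 a week), with 19% to 38% screening positive (assumed from the Background: CMD 19-23%, violence 15%, full to no overlap) and full consent, the invited fraction is p + 0.33(1 - p) = 0.457 to 0.585. Then 20/0.585 = 34.2 to 20/0.457 = 43.7 screens a week are needed, or 0.494 to 0.632 of visits. s1 = 0.286 x 0.494 = 0.14 to 0.370 x 0.632 = 0.23.
- Overall, s1 = 0.142 to 0.370.

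**Bias model.** Let d0 and d1 be true nurse detection before and during, s0 the screened share at baseline, and h the share of nurse-missed positives recorded only because of the research screen:

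bias in change = h x [s1(1 - d1) - s0(1 - d0)]

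Assumed, not in the document: h = 0.1 to 0.5, d0 = 0.20, d1 = 0.60.

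- Screening starts with implementation (s0 = 0): 0.1 x 0.142 x 0.4 = +0.6 points to 0.5 x 0.370 x 0.4 = +7.4 points.
- All first-visit women screened at baseline (s0 = 1): 0.1 x (0.370 x 0.4 - 0.8) = -6.5 points to 0.5 x (0.142 x 0.4 - 0.8) = -37.2 points. The far end pairs full screening at baseline with the lowest later share. With full screening throughout recruitment and the two baseline weeks deducted, s1 = 9.25/39.3 to 12.55/39.3 = 0.235 to 0.319, and the bias is -6.7 to -35.3 points.
- The sign changes at s0 = s1 x 0.4/0.8 = s1/2, i.e. 0.07 to 0.19.

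**Simpler check, no true effect.** Suppose the research screen adds 5 to 20 points to recorded detection. Starting with implementation gives 0.286 x 5 = +1.4 to 0.370 x 20 = +7.4 points. Starting at full coverage in the baseline weeks gives (0.319 - 1) x 5 = -3.4 to (0.235 - 1) x 20 = -15.3 points averaged over implementation, and nothing during the recruitment weeks themselves.

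**Limits.** If h = 0, every figure is zero. The shares are for first visits, but neither review is restricted to first visits; if later visits count and the research screen acts only at the first, the figures shrink in proportion. They also assume the planned pace. A site at the selection minimum of 60 first visits a month (13.8 a week) could not enrol 20 a week, so screening there would run for longer.

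**The case against.** The strongest objection is that no mechanism is documented. Nothing says that fieldworkers alert nurses or refer women, and the numerators are nurse-completed records. The Background puts the gap down to nurses seldom screening; priming a woman does not make a nurse ask. This stands, and it is why no direction or size can be asserted. Nor does the article say that results are kept from nurses or that the research screen follows the consultation, so the possibility stays open.

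A reader might infer more in three places:
- **That the gain is inflated.** This needs screening to be absent or rare at baseline. The Cohort study's reference to baseline also allows a start in the baseline weeks, and the bias then turns negative.
- **That the short baseline proves unequal exposure.** Two weeks at 20 gives 40 women, 14% to 18% of the target, so at least 82% of recruitment falls outside it. That describes when recruitment happens, not the share of women exposed within each period.
- **That every screened woman receives the nurses' instrument.** The screen's stated thresholds are for the EPDS and a bespoke violence tool. The shared distress tool appears only in the Table 2 list of cohort instruments.

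It can also be said that screening data are already in REDCap, that relevant confounders could include this status, and that stratified reporting can be left to an analysis plan. That is largely fair. However, the within-day order of screen and consultation, and whether a fieldworker prompted a referral, cannot be recovered later if not noted at the time. Weekly monitoring helps, but a during-versus-after comparison is mixed with calendar trend. Cohort women are also interviewed again at 36 weeks, so exposure does not end cleanly with recruitment.

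**Conclusion.** The point holds as a low-severity, inexpensive improvement; it is not an error in the plan. The document supports three facts: a fieldworker screen for the conditions nurses must detect, an uncontrolled before-during comparison of nurse records without separation by that exposure, and a recruitment period that at the planned pace covers about 11 to 15 of 39 weeks. Exposure therefore differs between baseline and implementation unless screening runs throughout both.

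Whether this distorts anything depends on an undocumented effect of the research screen on disclosure or referral. Under assumed values (10% to 50% of missed positives recorded because of the screen; true detection rising from 20% to 60%), the bias runs from about -37 to +7 points averaged over implementation. That range shows only that the sign is open and that the size could matter; it is not an estimate.

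**What to change.** In REDCap, add to each MCR and referral record, in both periods, (1) whether the woman had been research-screened before that nurse consultation and (2) whether a fieldworker prompted the referral. Keep the planned pooled rates. Add a sensitivity report of detection and referral by period, with and without flagged women, and count research-prompted referrals separately.

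Do not require the research screen to follow the nurse consultation: that would move the baseline EPDS to after contact with the detection intervention. Recording the order is enough.

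The cost is one or two fields, completed by the facility's single fieldworker, who already does both tasks. The downside is that the unflagged subset in recruitment weeks will be small and possibly selected, so its rates should be read as a sensitivity check and not as a replacement for the pooled rates.

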## Background

Common mental disorders (CMDs), such as depression and anxiety, are highly prevalent during the perinatal period (pregnancy and the first year postpartum) in the Western Cape, South Africa. A facility-based study in Hanover Park, a low-income, residential suburb in Cape Town [1], reported that 21% of pregnant women were diagnosed with depression and 23% were diagnosed with anxiety [2]. Similar results were obtained from a study in Khayelitsha — a large peri-urban township settlement in Cape Town — where 19% of pregnant women screened positive for a CMD [3].

In low-resource settings such as these, the prevalence of domestic violence, poverty, and food insecurity is high. Interpersonal violence is ranked second in its contribution to the burden of disease in South Africa, and among women, intimate partner violence accounts for 62% of the burden of interpersonal violence [4]. Recent studies among perinatal women in Cape Town reported that approximately 15% of pregnant women experienced domestic violence during the past 12 months, more than 40% lived in food-insecure households, and food insecurity and domestic violence increased the risk of subsequently developing a CMD [2, 5–7]. Furthermore, perinatal CMDs have been associated with several adverse consequences for both mother and child, including preterm birth, low birthweight, and diminished mother-infant bonding [8, 9].

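### The measure named for judging clinical improvement counts only falls in EPDS, and no other cohort result is tied to that aim or stated to be weighted for the 33% sampling of screen-negative women

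*Protocol article*

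**What the plan says.** All points are in the protocol article, Cohort study section, unless stated otherwise.

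- The cohort has two uses: (i) to describe the presence of CMDs and domestic violence and their risk factors, and (ii) to judge whether the HSS interventions improved clinical outcomes. The next sentence reads: "It will be based on the proportion of women showing a clinically significant improvement as measured by the EPDS".
- The two definitions are "Women with an EPDS score of ≥13 at baseline will be classified as having symptoms of CMD" and "Clinically significant improvement will be classified as having a 50% reduction in EPDS scores", the latter at 36 weeks and at 6 weeks postnatal against baseline. There is no counterpart for worsening or onset. The text does not say whether the denominator is all cohort women or only those with EPDS ≥13 at baseline.
- All screen-positive women are invited, on "score ≥13 on the EPDS or ≥2 on the bespoke violence screening tool", so some of them have EPDS below 13. Also invited is "A random sample of 33% of pregnant women who screen negative".
- Follow-up covers everyone: "The presence of and risk factors for CMDs and experiences of domestic violence in cohort participants will be assessed again at the 36-week gestation", with the same at 6 weeks postnatal. It adds: "Changes in clinical outcomes and their risk factors will be assessed by comparing the 36-week gestation and the 6-week postnatal outcomes to the baseline outcomes".
- Linear regression of change in EPDS, adjusted for clinic and confounders, is added in the Data analyses section. That section does not mention the sampling fraction.
- The Background says that "food insecurity and domestic violence increased the risk of subsequently developing a CMD".

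**The concern.** Aim (ii) concerns a programme whose awareness and screening components reach all attenders. The Background leads one to expect some new cases in this population. Yet the one measure named for aim (ii) works in one direction. A woman who becomes a case is either outside its denominator or a non-improver like any other. If onset offsets recovery, the improvement proportion among baseline cases does not change.

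The other planned comparisons could show onset, but they have a difficulty of their own. The cohort over-represents women with high baseline scores by a factor of about three. High scores tend to fall and low scores tend to rise, so a cohort weighted towards high scores will on average appear to improve even when the clinic population is stable. An unweighted before-after comparison could therefore point the same way as the response measure for the same reason. Because the pilot is meant to inform a cluster randomised trial, a one-directional outcome could be carried into it.

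**Working it through.** The plan gives no figure for this point, so there is none to reproduce. The sample-size range does not bear on it.

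**1. Arithmetic without a distributional model**

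Inputs:
- Sampling fraction f = 0.33 (Cohort study).
- Share with EPDS ≥13, p = 0.21. This is an assumption: the Background gives 21% diagnosed with depression and 19% screening positive for a CMD, neither stated as EPDS ≥13.
- Recovery R = 0.40. This is an assumption: 40% of baseline cases halve their score and drop below 13, and no others leave the range.
- Simplifications: everyone below 13 is screen-negative, and uptake is equal.

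Onset I among women below 13 that exactly offsets recovery in the clinic population: p × R = (1 − p) × I, so I = 0.084 / 0.79 = 0.106.

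Unweighted cohort:
- Baseline prevalence = p / (p + f(1 − p)) = 0.21 / (0.21 + 0.2607) = 0.446.
- Follow-up prevalence = (p(1 − R) + f(1 − p)I) / 0.4707 = (0.126 + 0.0277) / 0.4707 = 0.327.

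In a cohort of 675 (3 × 225), about 301 women are cases at baseline and 374 are not. About 120 recover and 40 become cases, so 221 / 675 = 32.7% are cases at follow-up. The clinic population has not changed.

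The unweighted comparison breaks even only at I = 0.084 / 0.2607 = 0.322. Between 10.6% and 32.2% onset, the clinic population worsens while the unweighted cohort improves. At 20% onset, population prevalence is 0.126 + 0.79 × 0.20 = 28.4%, up from 21%. Unweighted cohort prevalence is (0.126 + 0.0521) / 0.4707 = 37.8%, down from 44.6%. The response proportion among baseline cases is 40% throughout.

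**2. Simulation**

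Two million pairs of normal scores per setting, rounded and limited to 0–30, with p = 0.19 or 0.21 and r = 0.3, 0.4 or 0.5 (the 0.3–0.5 range is from the sample-size paragraph). Mean EPDS is not in the protocol, so 6, 8 and 10 were tried. SD = (12.5 − mean) / z(1 − p); at mean 8 this is 4.5 / 0.878 = 5.13 or 4.5 / 0.806 = 5.58.

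| Result | No true change, mean 6–10 | +2 points in women below 13 at baseline, mean 8 |
|---|---|---|
| Baseline cases whose EPDS halves | 3–47% (20–34% at mean 8) | 20–34%, as under no change |
| Unweighted cohort prevalence | 42–45% to 23–28% | 42–45% to 29–34% |
| Unweighted mean EPDS change | −2.2 to −0.6 | −0.5 to +0.15 |
| Weighted prevalence | 19–21%, flat | 19–21% to 28–30% |

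Under no true change, 55–68% of women at 13 or more at follow-up were below 13 at baseline. The raw mean change stands in for the planned regression, whose full specification is not given.

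**3. Denominator**

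If the denominator were all cohort women, the +2-point scenario would move the improvement proportion (about 25% to 19% at mean 8, p = 0.19, r = 0.3). Onset would still have no count of its own, and a fall from 4 to 2 would count as improvement.

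**The case against.** The strongest reply is that onset is not hidden. The Cohort study section reassesses CMD in all participants and compares follow-up with baseline, and the Data analyses section models EPDS change without restricting it to baseline cases. This stands. A reader might infer that women who develop symptoms never enter the clinical conclusion; the text does not support that.

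Screen-negative women also serve use (i), which needs women without CMD for comparison. A reader might infer that enrolling them is inconsistent with the response measure, or that they are wasted; neither follows.

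The counselling is aimed at women with symptoms, so response among them is a reasonable measure to keep. That a fall from 14 to 8 is not a response shows only that response and remission differ; it is not an error.

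The simulated figures depend on an assumed mean EPDS, and the 2-point rise is hypothetical. The Background reports a substantial postnatal reduction in symptoms in both arms of the earlier trial. The 55–68% of new threshold crossings arise with no true change, partly as regression to the mean, so they are not evidence of real incidence being missed.

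Finally, a condensed article may leave weighting to an analysis plan. If a fuller plan weights the comparison, that part is met. What remains is in the article itself: it names one measure as the basis of the assessment, does not fix its denominator, and does not tie the two-directional analyses to aim (ii).

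**Conclusion.** The point holds in a limited form. The measure named for aim (ii) counts improvement only and has no count for onset. The analyses that could show onset are not stated to decide aim (ii). As described, they are also not weighted for unequal sampling, so an unweighted cohort result can show improvement when the clinic population is unchanged or worse.

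The direction of that distortion follows from the sampling design: whenever recovery and onset balance in the population, giving onset a third of its weight produces an apparent fall. Its size is an illustration. It is about 12 percentage points in the hand calculation (44.6% to 32.7%), and 42–45% to 23–28% in the simulation with no true change. Both rest on 19–21% having EPDS ≥13. The hand figure also assumes 40% recovery; the simulation assumes normal scores and r of 0.3–0.5. The 3–47% range for chance response shows how strongly that measure depends on an unknown mean. None of this says that onset will be high in this study.

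**What to change.** - Keep the 50% EPDS response as a result for aim (ii), and state that its denominator is women with EPDS ≥13 at baseline.
- Beside it, report the change in prevalence of EPDS ≥13 from baseline to 36 weeks and from baseline to 6 weeks postnatal in the whole cohort. Weight screen-positive women by 1 and sampled screen-negative women by 1/0.33 ≈ 3.03.
- Show the two parts separately: remission (≥13 to <13) and onset (<13 to ≥13).
- State that the aim (ii) conclusion is drawn from both results, and that an uncontrolled before-after change still includes the natural course of symptoms.

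This changes only the analysis wording; the scores and the sampling fraction are already held. The cost is precision. By the Kish approximation at p = 0.21, the variance factor is mean(w²)/mean(w)² = (0.446 × 1 + 0.554 × 9.18) / (0.446 × 1 + 0.554 × 3.03)² = 5.53 / 4.51 = 1.23, so the interval is about 11% wider. Weighting does not remove confounding by time, and the weights assume similar uptake in the two screening groups unless uptake is also taken into account.
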